#### 2.12.2 Secondary Outcome

All the secondary outcomes will be summarized in Mean ± SD and analyzed by repeated measurement analysis of variance.

In addition, scores of DAS28, CDAI, and SDAI will be classified as disease remission, low disease activity, moderate disease activity, and high disease activity according to the relevant definition (Prevoo et al., 1995; Aletaha and Smolen, 2005). The categorical data will be performed by chi-square tests by row sums (different disease activities) and column sums (groups).

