### 2.8 Sample Size

Based on the primary outcome, we use the model of “tests for two proportions” in PASS 15.0. Alternative hypothesis: two-sided. Test type: Z-test (unpooled). Power was set at 0.9 and alpha was set at 0.05. The intervention group and control group were allocated a 1:1 ratio. The effect size of the treatment group (P1): based on the results of our former small sample of observational study (results unpublished), about 53.26% of patients would transit to RA after 1 year of TCM treatment. The effect size of the control group (P2): without any medication interventions, about 70% of early-stage UA patients with ACPAs meet the 1987 ACR criteria 1-year follow-up (Firestein et al., 2016). We would need 173 subjects in each group. Predicting a 10% dropout rate, the subjects rise to 385. Considering there were 13 centers that took part in the studies, the final subject was set at 390 (30 subjects per center).

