#### 2.12.3 Safety Outcome

Safety outcomes in ITT data will be summarized according to the different SOC with CTCAE grades. Every category of AEs will be performed by chi-square tests by row sums (different CTCAE grades) and column sums (groups). In addition, we would screen out the YQCF-unrelated AEs to validate the safety of YQCF. The data will be summarized and analyzed as the methods mentioned above.

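### The supplementary tables of ordered disease-activity categories and AE grades are tested with a chi-square that ignores the ordering; an ordered test would be a cheap, minor improvement

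*Protocol article*

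**What the plan says.** Section 2.12.2 of the protocol article begins with the main analysis of the secondary outcomes: "All the secondary outcomes will be summarized in Mean ± SD and analyzed by repeated measurement analysis of variance". It then adds a categorical analysis in which DAS28, CDAI and SDAI are "classified as disease remission, low disease activity, moderate disease activity, and high disease activity". The test for that table is named: "The categorical data will be performed by chi-square tests by row sums (different disease activities) and column sums (groups".

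Section 2.12.3 names the same test for safety: "Every category of AEs will be performed by chi-square tests by row sums (different CTCAE grades) and column sums (groups".

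The article names no trend test, rank test or ordinal model for either table. It gives no category distribution, target effect or power for them. Its only power statement, in section 2.8, concerns the primary outcome.

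**The concern.** Both classifications are ordered by construction. Remission is better than low activity, low is better than moderate, and so on; CTCAE grades rise with severity. A row-by-column Pearson chi-square treats the rows as labels, so shuffling them leaves the p-value unchanged. With four activity categories and two arms it spreads its sensitivity over 3 degrees of freedom, although the question is mainly directional: does activity move down, or AE severity up, on YQCF?

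What is at stake is efficiency. If the effect is a general shift along the scale, a test that uses the ordering detects it more often with the same patients and data. In the AE tables, lower sensitivity makes a finding of no difference more likely, and section 2.12.3 names no other between-group test for them.

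Because the test is named in both sections, this is a stated choice and not a detail that the article leaves to a fuller document.

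**Working it through.** **1. The plan's own figure.** Section 2.8 gives the inputs "Alternative hypothesis: two-sided", "Test type: Z-test (unpooled", "Power was set at 0.9 and alpha was set at 0.05" and "The intervention group and control group were allocated a 1:1 ratio", with rates of 53.26% and 70%.

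n per arm = (z₀.₉₇₅ + z₀.₉₀)² × [p₁(1−p₁) + p₂(1−p₂)] / (p₁−p₂)² = 10.507 × 0.45894 / 0.028023 = 172.08, rounded up to 173.

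Dropout: 2 × 173 = 346, and 346 / 0.90 = 384.4, rounded up to 385.

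Both stated figures reproduce. I use 173 per arm for disease activity and 390 / 2 = 195 per arm for AEs.

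**2. Cost of 3 df against 1 df.** Suppose the whole effect lies along the ordering. The 1-df ordered test and the 3-df chi-square then have the same noncentrality λ. I choose λ to give the stated 1-df power at alpha 0.05, then compute P(χ²₃(λ) > 7.815).

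| Ordered test, 1 df | λ | Chi-square, 3 df | Loss (points) |
|---|---|---|---|
| 50% | 3.84 | 34.5% | 15.5 |
| 60% | 4.90 | 43.2% | 16.8 |
| 70% | 6.17 | 53.1% | 16.9 |
| 80% | 7.85 | 64.5% | 15.5 |
| 90% | 10.51 | 78.4% | 11.6 |
| 95% | 13.00 | 87.1% | 7.9 |

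**3. Simulation, disease activity.** Pearson chi-square on the 4×2 table against the tie-corrected Wilcoxon rank-sum test, 173 per arm, 40,000 replicates, no baseline adjustment. The five control distributions over the four ordered categories are assumed: (10, 20, 50, 20), (20, 30, 40, 10), (25, 25, 25, 25), (5, 15, 60, 20) and (40, 35, 20, 5) percent. The effect is an exact proportional-odds shift.

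| Odds ratio | Rank test | Chi-square | Loss (points) |
|---|---|---|---|
| 1.0 (type I error) | about 5% | about 5% | 0 |
| 1.5 | 48-55% | 33-39% | about 16 |
| 1.65 | 66-74% | 49-57% | about 17 |
| 1.75 | 75-83% | 58-68% | 15-17 |
| 2.0 | 91-95% | 79-86% | 8-12 |

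At an odds ratio of 1.6, the assumed distribution (15, 25, 40, 20) gives about 50% for the chi-square and 67% for the rank test.

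**4. Non-monotone differences.** The ranking of the tests can reverse. With control (10, 20, 50, 20) and treatment (15, 13, 57, 15) percent, the chi-square has 54% power and the rank test 10%. With (10, 30, 40, 20) against (20, 20, 40, 20), it is 73% against 10%.

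**5. AE grades.** 195 per arm. The assumed control distributions, read as no event and then rising grades, are (85, 10, 4, 1), (95, 3, 1.5, 0.5) and (70, 20, 8, 2) percent. The shifts toward higher grades correspond to odds ratios of 0.6, 0.5, 0.4 and 0.33 for being in a lower category. The chi-square loses from 0.1 points (both tests near 100%) to 19.6 points (47.3% against 66.9%). Its type I error is 3.3% to 4.8%, so it is slightly conservative in the sparsest table.

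**The case against.** **The categorical table is not the main analysis.** Section 2.6.2 defines the endpoints as changes in DAS28, CDAI and SDAI, and section 2.12.2 first analyses them as continuous scores. A reader might infer that three secondary endpoints depend on a weak test with no direction. They do not: the ANOVA keeps ordering and direction, and even in the categorical table the arm counts show which way a difference goes. This stands, and it removes most of the efficacy impact.

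**The power loss is not a property of the plan.** A reader might quote a flat loss of about 15 points. The article gives no distribution or effect from which such a figure could follow. A proportional-odds shift is also the kind of alternative that favours the rank test. This stands too, so only a conditional range can be given.

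**For AEs, ignoring the ordering is not plainly a mistake.** Under section 2.5, mild and moderate AEs lead to a change in the granules while severe AEs stop the intervention, so a difference confined to some grades is plausible. The chi-square can see such a pattern and a trend test may miss it. This stands, and argues for adding a trend test there and against replacing the chi-square.

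**Effect measures and exact methods are details often left to a fuller document.** Agreed: their absence is no fault. They appear under the fix only because they go with the ordered test. The named unordered test remains a stated choice that can be improved.

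**Conclusion.** The point holds as a cheap improvement of minor severity. Sections 2.12.2 and 2.12.3 assign an unordered test to ordered categories.

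For disease activity the cost is roughly 8 to 17 points of power. This assumes a proportional-odds shift, about 173 per arm, alpha 0.05, the category distributions listed above, and an ordered test with about 50-95% power. For AE grades the range is about 0 to 20 points, depending on the assumed rates and shift. If the true difference is not monotone, the chi-square can be the stronger test.

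A reader might also infer that the planned tests are invalid or that the trial's main conclusions are at risk. The documents support neither. Type I error stays at or below about 5%, and the primary outcome, the sample size and the repeated-measures analysis do not depend on these tables.

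**What to change.** **Section 2.12.2:** compare the activity categories between arms with a Wilcoxon rank-sum (linear-by-linear) test, or with a proportional-odds model adjusted for baseline category. Report the common odds ratio with its 95% CI next to the category counts.

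**Section 2.12.3:** keep the chi-square and add an ordered (trend) test across CTCAE grades, using exact versions where tables are sparse. State in advance that the two tests answer different questions: a general shift in severity, and any difference in the grade pattern.

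**Cost:** a line or so of analysis wording in each section, with no new data and no change to trial conduct. The ordered test is less sensitive to non-monotone differences. In the AE tables, running two tests instead of one adds to the number of comparisons, so they should be read as descriptive support.

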#### 2.12.3 Safety Outcome

Safety outcomes in ITT data will be summarized according to the different SOC with CTCAE grades. Every category of AEs will be performed by chi-square tests by row sums (different CTCAE grades) and column sums (groups). In addition, we would screen out the YQCF-unrelated AEs to validate the safety of YQCF. The data will be summarized and analyzed as the methods mentioned above.

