## Abstract

**Introduction:** Rheumatoid arthritis (RA) is an autoimmune disease characterized by progressive bone erosion on diarthrodial joints. RA patients usually experienced three stages before final diagnosis: the health period, the pre-clinical period (immune response exists without clinical symptoms), and the pre-RA period (immune response exists with mild inflammatory manifestation). Presently, there is seldom guidance referring to early intervention which is a benefit for stable disease conditions and low morbidity. Prophylactic treatment is a major feature of traditional Chinese medicine (TCM). In this present study, a multi-center, double-blind, placebo-controlled clinical trial is carried out to evaluate both efficacy and safety in preventing RA progression on Yunpi Qufeng Chushi formula (YQCF).

**Method:** The multi-center, double-blind, placebo-controlled clinical trial is conducted in 13 hospitals nationwide. A total of 390 patients ages between 18 and 70 will be recruited in the trial. They will be randomly assigned to the intervention group (YQCF) and placebo group. The follow-up visit will be taken every 3 months from baseline to 1 year. Diagnosis, disease activity scores, clinical disease activity index (CDAI), simplified disease activity index (SDAI), TCM syndrome scores, and safety assessments will be recorded at every visit. Joint color doppler ultrasound, health assessment questionnaire-disability index (HAQ-DI), and functional assessment of chronic illness therapy-fatigue (FACIT-F) will be recorded at baseline and the last visit.

**Discussion:** This work will provide evidence of YQCF in preventing RA progression. However, whether early intervention would benefit the controlling RA disease still needs a long-term follow-up.

**Ethics and dissemination:** Protocol version 2 (201910-1). This research was approved by the medical ethics committee of Zhejiang Chinese Medical University (2019-045). Results will be published in a peer-reviewed academic journal.

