#### 2.6.3 Safety Outcomes

AEs will be monitored for 48  weeks from the time when the subject signed the informed consent and enrolled in the trial to the last follow-up. Especially, visit 2 (4 weeks ± 2 days) is set to monitor the AEs. The description of severity (grades) and system organ class (SOC) of AEs will follow the Common Terminology Criteria for Adverse Events (CTCAE) Version 5.0 (SERVICES, 2017). The AEs would be coded using the current version of the Medical Dictionary for Regulatory Activities (MedDRA). The relationship between AEs and intervention will be judged according to the adverse drug reaction report and testing manual published by the Department of Drug Safety Supervision, State Food and Drug Administration of the People’s Republic of China (Guan et al., 2008).

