### 2.13 Data Monitoring, Harms, and Auditing

Zhejiang Chinese Medical University led a steering committee and data monitoring committee (DMC) which is composed of experienced clinical researchers and academic investigators in this field. The committee will carry every month online and half a year of on-site auditing. The committee will oversee the data and safety of the study and will conduct primary outcome interim analyses using Lan-DeMets with O'Brien Fleming to oversee the efficacy and safety when it reaches 50% of the recruitment. Moreover, the committee would assess the status and quality of the study, such as the rate of recruitment and withdrawal. Overall, the YGCG is relatively safe, and the AEs are mild. Every patient and their family members could report any AEs/conditions to the investigators via WeChat and the investigators would immediately take action.

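### The only stated adverse-event test compares the CTCAE grade mix among events that occurred, not how many patients in each arm had an event

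*Protocol article*

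**What the plan says.** The Abstract makes safety a trial objective alongside efficacy: the trial is "carried out to evaluate both efficacy and safety in preventing RA progression".

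Section 2.12.3 then has three parts.

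- A descriptive summary: "Safety outcomes in ITT data will be summarized according to the different SOC with CTCAE grades".
- One test, with its layout: "Every category of AEs will be performed by chi-square tests by row sums (different CTCAE grades) and column sums (groups").
- A second pass restricted by causality, in which "we would screen out the YQCF-unrelated AEs to validate the safety of YQCF", followed by "The data will be summarized and analyzed as the methods mentioned above". The same test is therefore used again.

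Section 2.6.3 confirms that the rows are severity grades of events: "The description of severity (grades) and system organ class (SOC) of AEs will follow the Common Terminology Criteria for Adverse Events (CTCAE) Version 5.0". Section 2.13 says the monitoring committee "will conduct primary outcome interim analyses using Lan-DeMets with O'Brien Fleming to oversee the efficacy and safety when it reaches 50% of the recruitment"; that analysis concerns the primary outcome, and no comparison of AE incidence is named there. I found none elsewhere in the article.

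**The concern.** A chi-square test on a grade-by-arm table asks whether the distribution over grades is the same in the two columns. If the columns hold only AEs, or only patients who had an AE, the column totals are taken as given and the number of patients affected drops out of the question. An excess of AEs on YQCF with a similar grade mix is then invisible to the test.

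The layout seems to follow the one in section 2.12.2, where "scores of DAS28, CDAI, and SDAI will be classified as disease remission, low disease activity, moderate disease activity, and high disease activity". There it works, because every assessed patient falls in one of the four rows. CTCAE grades do not cover every patient in that way.

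There is also a degenerate case. If all AEs in a category share one grade, the table has a single row and no test can be computed, even if every event is on YQCF. Section 2.13 expects AEs to be mild, so little spread over grades is plausible in many categories.

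At stake is the conclusion that section 2.12.3 wants to draw about YQCF. A non-significant result from the test as worded says nothing about whether more patients had AEs on YQCF.

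**Working it through.** **Inputs.** Total sample 390 with 1:1 allocation (section 2.8), so 195 per arm. Table layout from section 2.12.3. The article gives no AE rates or grade mix and no figure for the AE test, so there is nothing of the plan's own to reproduce here and all AE counts below are assumed. All tests are Pearson chi-square without continuity correction unless stated.

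**Base case.** 30 of 195 patients with an AE on YQCF and 10 of 195 on placebo; 20% grade 2 and 80% grade 1 in both arms.

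| | YQCF | Placebo |
|---|---|---|
| Grade 1 | 24 | 8 |
| Grade 2 | 6 | 2 |
| No AE (not stated in the plan) | 165 | 185 |

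1. *As worded, first two rows only.* The expected counts equal the observed counts (for example 8 × 10 / 40 = 2), so chi-square = 0.00 on 1 df and p = 1.00.
2. *Incidence, any AE against none.* Chi-square = 390 × (30 × 185 − 10 × 165)² / (40 × 350 × 195 × 195) = 11.14 on 1 df, p = 0.0008 (Fisher's exact p = 0.0013).
3. *Risk difference.* 30/195 − 10/195 = 0.103. Standard error = √[(0.154 × 0.846 + 0.051 × 0.949)/195] = 0.030. Wald 95% CI 0.043 to 0.162.
4. *All three rows.* Chi-square = 11.14 on 2 df, p = 0.0038.

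**Does this depend on equal grade mixes?** Keep placebo at 2 of 10 grade 2 and let k of the 30 YQCF AEs be grade 2. Incidence stays at p = 0.0008 throughout.

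| k of 30 | 0 | 1 | 6 | 12 | 15 | 16 | 17 |
|---|---|---|---|---|---|---|---|
| Worded test, p | 0.012 | 0.083 | 1.00 | 0.25 | 0.097 | 0.067 | 0.044 |

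The worded test stays above 0.05 for every k from 1 to 16, a grade-2 share on YQCF of 3% to 53%. With the no-AE row added, p lies between 0.0011 and 0.0038 over the same range.

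**Smaller excess, 15 against 5, same 20% grade 2.** Worded table (12, 4; 3, 1): p = 1.00. With a no-AE row (180, 190): chi-square = 5.27 on 2 df, p = 0.07. Incidence: chi-square = 5.27 on 1 df, p = 0.02 (Fisher 0.036).

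**Simulation.** 10,000 trials per scenario, true incidence 20% on YQCF and 10% on placebo, placebo grade-2 share 20%. Percentage of trials with p < 0.05:

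| Grade-2 share on YQCF | 10% | 20% | 30% | 40% | 50% |
|---|---|---|---|---|---|
| Worded test | 20 | 5 | 12 | 33 | 63 |
| With no-AE row | 77 | 70 | 74 | 83 | 92 |
| Incidence | 79–80 | 79–80 | 79–80 | 79–80 | 79–80 |

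With a common grade mix the worded test rejects at its nominal 5%, although incidence is doubled. A separate simulation (4,000 trials, three grades in the proportions 60/30/10 in both arms) agrees: 5.4% for the worded test against 80.9% for incidence.

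**The reverse case.** With 40 patients with an AE in each arm but grade counts of 30/8/2 against 10/25/5, the worded test gives p = 0.00004 and incidence p = 1.00. The two tests answer different questions.

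**The case against.** The best counter-argument is that section 2.12.3 opens by referring to ITT data. An ITT set includes every randomised patient, so an analyst cross-classifying patients by grade and arm might well add a row for those without an event, as the parallel wording in section 2.12.2 suggests. On that reading the test does respond to incidence. In the base case the decision at 0.05 is the same as for a direct incidence test, and when grade mixes differ enough (40–50% against 20% grade 2) it is the stronger of the two. This much stands. But the ITT reference sits in the sentence on the summary, while the sentence on the test lists only CTCAE grades as rows. Even with the extra row, the test loses power when grade mixes are similar, and in the smaller example this changes the decision (0.07 against 0.02).

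A second objection is that details such as worst-grade counting and confidence intervals normally belong in an analysis plan or table shells. That is fair for those details taken alone. The core point is different: the article fixes the rows and columns of the test, and an analysis plan that follows it inherits the problem.

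Third, the consequence is limited. The summary by organ class and grade would show an excess to anyone who knows the arm sizes, and the article sets no safety hypothesis or threshold. That also stands, and it limits how serious the point is. Finally, part of the 1-to-16 range reflects low power with only 10 placebo AEs and not the layout alone; the equal-mix result does not depend on that.

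**Conclusion.** The concern holds. As worded, the only AE test in the article compares severity among events and does not compare how many patients were affected. For an assumed 30 against 10 of 195 with equal grade mixes it returns p = 1.00, where incidence gives p = 0.0008 and a risk difference of 10.3 points. At 20% against 10% true incidence with a common mix, it rejects in about 5% of trials against about 80%.

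This rests on the literal table layout and on assumed AE counts and grade mixes. If a no-AE row was meant, the flaw shrinks to a loss of power when grade mixes are similar (70–77% against about 80% at YQCF grade-2 shares of 10–30%). The descriptive counts are unaffected. The change should be made, because section 2.12.3 reuses this test when it seeks to establish the safety of YQCF.

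**What to change.** Reword section 2.12.3 along these lines:

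- For each AE category, compare between arms the number of ITT patients with at least one AE (any grade, and grade 3 or above), counting each patient once at worst grade. Use a chi-square or Fisher's exact test and report the risk difference with a 95% CI.
- Keep the grade-by-arm table as a descriptive summary.
- Apply the same method to the analysis that leaves out AEs judged unrelated to YQCF.

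The cost is wording in section 2.12.3 only. No new data are needed, and the sample size is unaffected.

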#### 2.12.4 Subgroup Analysis

The subgroup analysis of the primary outcome and the secondary outcome will be based on anti-CCP positive or negative.

### 2.13 Data Monitoring, Harms, and Auditing

Zhejiang Chinese Medical University led a steering committee and data monitoring committee (DMC) which is composed of experienced clinical researchers and academic investigators in this field. The committee will carry every month online and half a year of on-site auditing. The committee will oversee the data and safety of the study and will conduct primary outcome interim analyses using Lan-DeMets with O'Brien Fleming to oversee the efficacy and safety when it reaches 50% of the recruitment. Moreover, the committee would assess the status and quality of the study, such as the rate of recruitment and withdrawal. Overall, the YGCG is relatively safe, and the AEs are mild. Every patient and their family members could report any AEs/conditions to the investigators via WeChat and the investigators would immediately take action.

## 3 Ethics and Dissemination

This trial has been approved by the Zhejiang Chinese Medical University Ethics Committee under number 2019-045. Approval has been obtained from the local institutional review boards at all participating centers. The results of RCT will be published in peer-reviewed journals. All subjects were required to obtain permission to publish the results of the study and to ensure anonymity and confidentiality. All data will be processed under the rules of the government and law. All researchers will guarantee the anonymity of patients and will not disclose the names of patients in forms, reports, or articles unless required by law. Only authorized individuals can obtain patient information.

